#### Computer-tailored advice

Participants will receive a computer-tailored advice to increase awareness of their lifestyle [22]. Awareness is found to be an important mediator of participation in health promotion programmes [23]. The benefits of computer tailoring is attributed to the fact that individualized feedback commands greater attention, is processed more intensively, contains less redundant information, and is appreciated better than the provision of general documentation [24].

After baseline measurements the participant in the intervention group will receive an email with the notification that a personal advice is available on the Health Portal. Considering the answers on the questionnaire filled out at baseline a personal advice on PA, fruit and vegetable consumption, and fat intake will be generated. The advice aims to increase adherence to the intervention and to motivate the participant to engage in PA and a healthy diet, and consists of the following parts:

1) Personal feedback: feedback on to what extent the recommendations on PA and dietary intake are met.

2) Action feedback: feedback on the specific barrier attributed by the participant as most important to not meeting the recommendations. The advice also contains opportunities to link to further information on the Health Portal and provides tips on how to meet the guidelines.

If one meets the recommendations, only the personal feedback is provided. See Figure 2 for an example of the computer tailored advice.

**Figure 2 F2:**
[figure not shown]
Example of the flow to a computer tailored advice.

#### Monitoring function

Second, a monitoring function is integrated in the Health Portal to increase adherence to the intervention programme and consequently increase compliance with the lifestyle recommendations and sustainability of healthy behaviour. Recent studies have shown that people who want to change their lifestyle should be encouraged to regularly monitor their progress in adopting a new behaviour [25,26].

With the monitor function individual progress charts on self-reported weight, BMI, PA, and fruit and vegetable intake will be generated. The results of the baseline measurements will be used as starting point. The frequency of the use of this monitoring function is at the discretion of the participant. After 12 months the progress will be evaluated and communicated as part of the intervention. See Figure 3 for an example of a progress chart.

**Figure 3 F3:**
[figure not shown]
Example of the flow to a progress chart (monitoring function).

#### Personal Coach

The third critical feature of the Portal is a personal coach who will give continuous feedback and support through monthly emails. As like the monitoring function, this feature is part of the Health Portal to increase adherence to the intervention programme and to motivate participants to comply with the lifestyle recommendations and/or to maintain a healthy lifestyle. A previous study found promising results of individualized, interactive support for behaviour change on lifestyle [27].

Three groups of participants will be distinguished, based on Health Portal use and lifestyle. First, participants who do meet the recommendations on PA and/or fruit and vegetable intake at baseline will receive automatically generated emails with support to maintain their healthy lifestyle. Second, those not meeting the recommendation and not using the Health Portal will receive a reminder, a single question whether they have changed their behaviour and an invitation to use the monitoring function. Last, participants who use the monitoring function, but did not meet the recommendation at baseline, will receive a personal, not automatically generated, email with feedback on the data imported in the monitor.

If the participant does not want to receive the monthly emails, he can indicate this on the Health Portal.

#### Contact with professionals

The fourth feature is the opportunity to seek personal advice from a variety of professionals. By sending a message via the Health Portal participants can consult several experts such as a personal coach, a physiotherapist, or a dietician. This function is added to the Portal to increase adherence to the intervention programme.

The complete Health Portal will be offered for 12 months. After 12 months the monthly contact by a personal coach will be terminated, but access to the Portal will remain throughout the project.

### Measurements

#### Primary outcomes

##### Physical activity

PA level will be assessed by the self-administered short version of the International Physical Activity Questionnaire (IPAQ) [28]. The IPAQ consists of seven open-ended questions providing information on the time spent on walking, moderate- and vigorous intensity activities and in sitting in the past seven days. Participants will be instructed to refer to all domains of PA. Frequency per week and duration per day spent on the specific activity will be assessed. Concerning sitting, only duration per day will be assessed.

Both categorical and continuous indicators of PA will be calculated. By multiplying the metabolic-equivalent (MET) intensity for each activity with the weekly duration (in minutes) spent on each activity, the continuous measure (MET-minutes per week) will be calculated as recommended in the IPAQ scoring protocol [28]. The Dutch national guideline for PA stipulates that an adult should engage in PA of at least moderate intensity for at least 30 minutes a day on five days a week, and preferably every day [3]. As a categorical measure, compliance with the recommended amount of PA is defined by spending a total of at least 150 minutes on walking, moderate-intensity and vigorous-intensity PA per week [29]. In addition, compliance with the recommendation of vigorous PA will be assessed by examining if one does engage in vigorous PA on at least 3 days a week for at least 20 minutes on these days.

##### Fruit and vegetables

Fruit and vegetable intake will be assessed by means of a self-administered nine-item validated Dutch Food Frequency Questionnaire [30]. The questionnaire consists of seven items on fruit consumption and two items on vegetable consumption. First, participants will be asked to indicate on how many days during the last month they ate or drank the most often consumed fruit and vegetables in the Netherlands (i.e. apples, citrus fruit, cooked vegetables, etc.). Answer categories vary from 'never or less than once a month' to '7 days a week'. For all answers except 'never or less than once a month' a closed question follows in which one is asked to indicate the number of serving spoons, pieces, or units of juice consumed on such a day.

Total fruit consumption and total vegetable consumption will be calculated in grams. The total scores will also be used to determine compliance with the recommendations of an average of 200 grams of fruit and 200 grams of vegetables a day.

#### Secondary outcomes

##### Self-efficacy

Self-efficacy concerning PA and fruit and vegetable intake will be determined by asking how confident participants are to engage in PA and fruit and vegetable consumption in the next month, rated on a Likert scale between 1 (certainly) and 5 (certainly not) [31].

##### Perceived barriers

Perceived barriers concerning PA and fruit and vegetable intake will be assessed, by asking for the most important barrier to engage in these behaviours. The question on barriers to engage in PA has the following answer categories: not enough time/too busy, do not enjoy sports, too expensive, tired, fear of injury, no facilities at home, no facilities in direct environment, lack of a partner to exercise with, health problems, unsafe environment, and no barriers. The question on barriers concerning fruit and vegetable intake has the following categories: not enough time/too busy, not tasty, too expensive, no facilities at work to buy fruit and/or vegetables, no availability in the shops in the home environment, and no barriers.

##### Fat intake

Fat intake will be assessed by means of a self-administered 35-item validated Fat list covering 19 (groups of) food products. Participants will be asked about the frequency of food items during the last month with fixed categories. For each of the 19 categories a fat score, ranging from 0 (lowest fat intake) to a maximum varying from 3 to 5 points (highest fat intake), will be determined. Scores on the Fat list are presented in points instead of grams of fat, as only the most important saturated fat sources were included in the questionnaire [32]. A total fat score (range 0 – 80) will be calculated by adding up the 19 category fat scores.

##### Cardiovascular risk profile and physical fitness

The risk profile for cardiovascular events will be assessed by the SCORE (Systematic Coronary Risk Evaluation) system, taking into account the following risk factors: sex, age, smoking, total cholesterol level, and systolic blood pressure [33]. Sex, age, and smoking will be assessed by questionnaire. During a health check total blood cholesterol level will be determined in non-fasting blood through a finger prick (Accutrend GC, Roche Company, Mannheim, Germany). Systolic blood pressure will be measured with a fully automated sphygmomanometer (Omron M4-I, Omron HealthCare Europe BV, Hoofddorp, the Netherlands). With this sphygmomanometer resting heart rate will be measured as well.

In addition to these measures length and body weight will be measured to determine BMI (kg/m^2^). Waist circumference and thickness of three skin folds (i.e. men: pectoralis major, abdomen, quadriceps; women: triceps, crista iliaca, quadriceps) will be measured to calculate body fat percentage.

A submaximal exercise test on a bicycle ergometer will be conducted to predict maximal oxygen uptake, according to the American College of Sports Medicine's (ACSM) protocol, using three-minutes stages and terminates at approximately 80% of the age predicted maximum heart rate. The initial test workload will depend on age, sex, and exercise status. The maximum number of workload stages is four, and the minimum test time is nine minutes. Participants will be asked to pedal with a frequency of 60 revolutions per minute (rpm). During the test, heart rate will be recorded, and used to predict maximal oxygen uptake (Vo_2_max). All the physical measurements will be done according to the guidelines for exercise testing of the ACSM [34].

#### Confounding variables

Possible confounders include demographics, smoking behaviour, and general health. The demographic variables of importance are age, ethnicity, educational level, sex, and marital status. Smoking is defined as current smoking status. General health will be assessed using the Short Form-12 questionnaire [35]. In addition, some questions on occupation will be asked: job title, years in current job, days and hours of work (including overtime work), main job requirements (physical or mental), and working conditions [36]. During a worksite visit, environmental determinants will be assessed, especially available resources in the company to provide and sustain healthy behaviour (e.g. fitness room, financial compensation for membership of sport/fitness club, stairs, fruit and vegetables in canteen). Further, participants will be asked if they have Internet availability at home.

### Process evaluation

#### Participation

In the non-response analysis the following characteristics of (non)participants will be considered: age, sex, education, job title. In addition, enterprise size (number of employees) and history of health promotion activities in the company will be considered.

#### Adherence and Sustainability

Adherence to the intervention programme will be analysed in relation to compliance with lifestyle recommendations on PA and on fruit and vegetable intake, and in relation to sustainability of a healthy lifestyle. As markers of adherence to the intervention programme, the frequency of visiting the Health Portal, duration of stay on the Portal and frequency of contacts with professionals and personal coach will be registered. This will be done for the full Health Portal, as well as separately for the different parts of the Health Portal.

In addition, characteristics of participants (demographic variables, lifestyle at baseline, job, social support from colleagues and friends, and Internet availability at home) will be analysed as to subgroups with the best adherence to the intervention programme, compliance with the lifestyle recommendations, and sustainability of a healthy lifestyle.

### Cost-effectiveness evaluation

The cost-effectiveness analysis will be performed from a societal perspective as well as a company perspective. The following direct costs will be determined: cost price of the standard WHPP, costs for the Health Portal and direct costs of medical consumption. Direct costs of medical consumption will be based on frequency of contacts with a variety of health professionals and average remuneration fee, assessed by an adapted version of the Dutch Trimbos and iMTA Questionnaire on Costs Associated with Psychiatric Illness (TiC-P) [37]. The direct costs will be measured over the complete follow-up period of 24 months with annual questionnaires with 12-month recall.

The indirect costs will be based on assessment of days with loss of productivity at work due to health problems and productivity loss due to sickness absence, using the Dutch productivity and disease questionnaire (PRODISQ) [38]. The estimated days of productivity loss will be multiplied by the average wage per day for each worksite.

In a second step cost-effectiveness ratios will be calculated on two measures of health: general health and the SCORE risk profile for cardiovascular events.

### Sensitivity analysis

The sensitivity analysis will start with the analysis of the effectiveness of the intervention in specific subgroups, most notably those workers with a low physical activity level, with a low intake of vegetables and fruit, and with a high body mass index. A sensitivity analysis will also be performed on the individual cost-effectiveness ratios by means of bootstrapping. This part of the sensitivity analysis will be used to determine the minimum level of effectiveness required to make the Health Portal more cost-effective than the standard WHPP.

### Sample size

The assumptions for the power calculations were: an intra-cluster correlation of 0.05 (as observed in a previous cluster RCT in companies [39]), an average of 20 workers per cluster, a power of 80%, and a level of significance of 5% (one-sided). Under these assumptions, we anticipate to be able to detect a difference of at least 12% in prevalence between intervention and control group (e.g. primary outcome measure 30% compliance with the recommendation for PA up to 42%) with 350 workers with completed questionnaires assigned to the intervention. Without a noticeable intra-cluster variance the detectable difference will increase by 9%. With an initial participation of 70% and loss-to-follow-up of 30%, the cluster RCT should invite 2*700 workers.

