## Background

### Cardiovascular disease

Cardiovascular disease (CVD) is the leading cause of disability and mortality in most Western countries. CVD causes nearly half of all deaths in Europe (49%) [1]. Major modifiable risk factors for CVD include smoking, alcohol use, low physical activity (PA), and poor nutrition. The prevalence of several risk factors is very high, most notably low PA and poor nutrition (low fruit and vegetable consumption and high saturated fat intake).

According to a survey in European Union countries in 2002, 56% of the Dutch population over 15 years was insufficiently physically active for health [2]. The Dutch recommendation on PA stipulates that an adult should engage in PA of at least moderate intensity for at least 30 minutes a day on five days a week, and preferably every day in order to obtain health benefits [3]. In 2006, about half of the Dutch adults (25–55 year) met this recommendation [4]. In order to improve physical fitness it is recommended to engage in PA of vigorous intensity for at least 20 minutes on at least three days a week [3]. Exercise capacity has been found to be a powerful predictor of mortality [5]. It has been estimated that the life expectancy for people with low PA levels at age over 50 is 1.4 years less than for people with moderate PA levels and even 3.8 years less than for people with high PA levels [6].

The results of a recent meta-analysis on cohort studies indicate that fruit and vegetable consumption is inversely associated with the occurrence of coronary heart disease. The risk of coronary heart disease decreased by 4% for each additional portion of fruit and vegetables per day [7]. In the last representative Dutch food intake survey in 1997/1998 less than a fourth of the Dutch population met the recommendation for vegetable (200 grams a day) and fruit intake (200 grams a day) [8]. Regarding saturated fat intake, only 9% of the Dutch adult population met the recommendation (a maximum of 10 percent of energy intake as saturated fat) in 1997/1998 [9]. A high intake of saturated fat increases the risk of coronary heart disease [10].

The imbalance between PA and nutrition is an important cause of overweight and obesity, which in turn are important risk factors for CVD [11]. In the Netherlands self-reported overweight (body mass index ≥ 25) in adult men increased from 37% in 1981 to 51% in 2004, and in adult women from 30% in 1981 to 42% in 2004 [12].

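### The 30% physical-activity compliance used to illustrate power has no support in the protocol, whose own figures are 44% to about 50%; there, power for 12 points is about 74%, against 77% at 30% by the standard formula and 80% as stated

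*Protocol article*

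**What the plan says.** The Sample size section assumes "an intra-cluster correlation of 0.05 (as observed in a previous cluster RCT in companies [39"), "an average of 20 workers per cluster", 80% power and "a level of significance of 5% (one-sided"). With 350 completed questionnaires in the intervention arm it expects to "detect a difference of at least 12% in prevalence between intervention and control group". The only worked example is "e.g. primary outcome measure 30% compliance with the recommendation for PA up to 42" percent. No source is given for the 30%.

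Two figures elsewhere in the article bear on that rate, both in the Background under Cardiovascular disease:

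- 2002: "56% of the Dutch population over 15 years was insufficiently physically active for health", which leaves 44% sufficiently active.
- 2006: "about half of the Dutch adults" aged 25 to 55 met the Dutch recommendation of 30 minutes of at least moderate activity on five days a week.

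The Physical activity section under Primary outcomes then scores compliance as "spending a total of at least 150 minutes on walking, moderate-intensity and vigorous-intensity PA per week", with no condition on the number of days.

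**The concern.** Compliance with the PA recommendation is a primary outcome, and the power statement for it rests on a control rate well below both rates that the article reports. The 2006 figure is the closer match: it covers working-age adults in the year before data collection starts. The trial's definition widens the gap, because anyone who meets 30 minutes on five days also reaches 150 minutes in total. In the same population the scored rate cannot be lower than the norm rate. Controls also receive a health check and advice under the standard programme, and nothing in the article points down towards 30%.

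The binomial variance is smaller at 30 v 42% than at 44 v 56% or 50 v 62%, so the example is computed at a more favourable point than the article's own data suggest. A null PA result would then be read against 80% power that the design does not have at those rates.

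**Working it through.** **Inputs.** From the Sample size section: intra-cluster correlation 0.05, 20 workers per cluster, one-sided 5%, 80% power, 350 completers in the intervention arm, difference 12 points. Equal arms are inferred from the 2 × 700 invitations. Control rates are 30% (Sample size), and 44% and 50% (Background).

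**Design effect and effective size.** 1 + (20 − 1) × 0.05 = 1.95, and 350 / 1.95 = 179.5 per arm.

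**Formula.** With unpooled variance, power = Φ(0.12 / √[(p₁q₁ + p₂q₂) / 179.5] − 1.645). The pooled version uses the average proportion under the null hypothesis and gives values about 0.4 points lower.

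**Reproducing the stated 80%, at 30 v 42%.**

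- Unpooled: p₁q₁ + p₂q₂ = 0.2100 + 0.2436 = 0.4536; standard error √(0.4536 / 179.5) = 0.0503; 0.12 / 0.0503 = 2.387; power = Φ(2.387 − 1.645) = 77.1%.
- Pooled 76.7%; arcsine 76.8%.
- Completers needed per arm for 80%: (1.645 + 0.842)² × 0.4536 / 0.12² × 1.95 = 380 unpooled, 384 pooled, against 350 stated.
- Control-rate variance in both arms, 2 × 0.30 × 0.70 = 0.42: 352 per arm, 79.8% power, detectable difference 12.0 points.

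Of the variants tried, only the last returns the stated figures. The article's 9% without clustering, read here as a detectable difference of 9 points, does not settle which formula was used: pooled gives 8.9 and the control-rate version 8.6.

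**At other control rates.** Same 350 per arm, design effect 1.95, one-sided 5%:

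| Control v intervention | Power, pooled | Power, unpooled | Power, control-rate variance | Detectable difference at 80%, pooled |
|---|---|---|---|---|
| 30 v 42% | 76.7% | 77.1% | 79.8% | 12.6 points |
| 44 v 56% | 73.7% | 74.1% | 74.1% | 13.1 points |
| 50 v 62% | 74.2% | 74.6% | 73.5% | 13.0 points |

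At 44% and 50% all three formulas fall between 73.5% and 74.6%. Completers needed per arm for 80% power by the pooled formula are about 417 and 412.

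**Above 50%, pooled.** Power for 12 points is 75.5% at 55%, 77.7% at 60%, 80.0% at 64% and 84.8% at 70%. The article gives no figure for this range.

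**Splitting the gap, pooled.** From the stated 80% to 76.7% at 30 v 42% is 3.3 points, before the control rate moves. From 76.7% to 73.7–74.2% is 2.5 to 3.0 points, due to the control rate. The detectable difference moves from 12.6 to 13.0–13.1 points, or 0.4 to 0.5.

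**Fruit and vegetables.** The Background says that less than a fourth met those recommendations. At 25 v 37%, power is 79.4% pooled and 79.8% unpooled.

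**The case against.** The strongest reply is that 30% is marked as an example within a general statement about prevalence differences. The 44% and 50% are national survey values, not rates among participating workers on the trial's questionnaire. There are other primary outcomes, and for fruit and vegetables the stated 80% is essentially right. The article also scores a second PA recommendation, on vigorous activity, for which it gives no rate. Finally, 350 completers and 12 points fit a single shortcut calculation, so this is a disputed planning assumption rather than a slip in arithmetic.

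Much of that stands. It softens the conflict but does not remove it: this is the only worked example, it names PA compliance as the primary outcome, and the article offers no figure near 30% for it.

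Three stronger readings are tempting, and the article does not support them:

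- **That the control rate explains the whole fall from 80% to 74%.** This is true only if the control-rate-variance shortcut was used, which the article does not say. By the standard formula about half of the fall is already there at 30 v 42%.
- **That power is about 74% at any control rate above 50% as well.** The 150-minute rule does argue for a higher rate, but power then rises. At 64% it is back at 80%.
- **That the shortfall should be quoted for a two-sided test.** The article specifies a one-sided test. Whether that is the right choice is a separate question, and two-sided figures would overstate what the control rate does.

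**Conclusion.** The point holds in a limited form. The 30% is unsupported by the article and sits below both of its own figures for PA compliance. At 44% to 50% in controls, 350 completers per arm give about 74% power for 12 points, or 80% power for about 13 points. The stated inputs of 30 v 42% give about 77% by the standard formula, and about 80% only with the control-rate variance in both arms. Replacing 30% by 44% to 50% costs about 3 points of power and about half a point of detectable difference by the standard formula.

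This rests on equal arms, an intra-cluster correlation of 0.05 that does not change with the control rate, and national rates as a guide to the workers enrolled. The effect is modest and does not call the design into question, but it concerns the power statement for a primary outcome and is worth correcting.

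**What to change.** In the Sample size section:

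1. Restate the PA calculation at a control rate of 44% to 50%: about 74% power for 12 points, or about 13 points at 80% power, with 350 completers per arm and a one-sided 5% test. If 30% is kept, give its source and explain why it differs from the Background.
2. Name the variance formula, so that the 80% at 30 v 42% can be reproduced or corrected to about 77%.
3. Show higher control rates, for example 55% to 70%, labelled as an assumption prompted by the looser 150-minute definition.
4. Give fruit and vegetables their own line at 25 v 37%: about 80%, one-sided.

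No extra workers are needed. The cost is a rewritten paragraph and a slightly less favourable stated figure for PA.

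### On the protocol's own inputs, 350 completers per arm give about 77% power for 30% versus 42%, not 80%, and the sentence on the detectable difference without clustering is reversed.

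*Protocol article*

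**What the plan says.** The Sample size section of the protocol article fixes all the inputs:

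- Clustering: "an intra-cluster correlation of 0.05 (as observed in a previous cluster RCT in companies [39" and "an average of 20 workers per cluster".
- Error rates: "a power of 80%, and a level of significance of 5% (one-sided".
- Target: "we anticipate to be able to detect a difference of at least 12% in prevalence between intervention and control group". The worked example is "primary outcome measure 30% compliance with the recommendation for PA up to 42" per cent.

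It then says that this is achieved "with 350 workers with completed questionnaires assigned to the intervention. Without a noticeable intra-cluster variance the detectable difference will increase by 9" per cent. Finally, assuming 70% participation and 30% loss to follow-up, it concludes that "the cluster RCT should invite 2*700 workers". The 350 is given for the intervention group only, but the factor of 2 on the invitations implies arms of equal size.

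**The concern.** Two statements in this paragraph do not follow from its inputs.

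First, the usual formula for two proportions, inflated by the design effect, does not return 350 for 30% versus 42%. The stated power would then be somewhat optimistic.

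Second, the paragraph says that the detectable difference gets larger when there is no intra-cluster correlation. Positive intra-cluster correlation reduces the effective sample size, so removing it must make a smaller difference detectable. As printed, the sentence tells the reader of a cluster trial that clustering helps.

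At stake is how far a reader can rely on the quoted power and detectable difference when judging the result, particularly a null one.

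**Working it through.** **Inputs (all from Sample size).** ICC 0.05; 20 per cluster; one-sided alpha 0.05 (z = 1.645); power 80% (z = 0.842); rates 0.30 and 0.42; 350 completers per arm; 700 invited per arm; 70% participation; 30% loss.

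**Design effect.** 1 + (20 - 1) x 0.05 = 1.95, taking the 20 as workers analysed.

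**Reproducing 350.** The only formula tried that comes close uses the control-arm variance in both arms:

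- n = (1.645 + 0.842)^2 x 2 x 0.30 x 0.70 / 0.12^2 = 180.3; x 1.95 = 351.6.
- On the same formula, the detectable differences at 350 are 12.0 points with clustering and 8.6 without.

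This probably explains the stated 350, 12 and 9. It understates the variance, because at 42% the variance is 0.42 x 0.58 = 0.2436, against 0.21 at 30%.

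**Required number with both variances.**

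- n = (1.645 + 0.842)^2 x (0.21 + 0.2436) / 0.12^2 = 194.8; x 1.95 = 379.8, so about 380 per arm.
- Other methods: pooled variance 384 to 385, arcsine about 384, continuity-corrected 418. None gives 350.

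**Power at 350 per arm.**

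- SE = sqrt(0.4536 x 1.95 / 350) = 0.0503.
- Power = Phi(0.12 / 0.0503 - 1.645) = 77.1%.
- The pooled-variance formula gives 76.7%. A cluster-level t test with 17 to 18 clusters per arm (350 / 20 = 17.5) gives 74% to 77%.

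**Detectable difference at 350 per arm, 80% power, from a 30% base.**

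- With clustering: 12.5 points (12.6 pooled).
- Without clustering (design effect 1): 8.9 points.
- The direction follows from the effective sample size, which rises from 350 / 1.95 = 179.5 to 350 per arm. Read literally, the printed sentence would give 12 + 9 = 21 points, or 12 x 1.09 = 13.1 points as a relative increase. Neither is possible.

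**Invitations.** 700 x 0.7 x 0.7 = 343 completers per arm, with power 76.4% (76.0% pooled). For exactly 350 one would invite 350 / 0.49 = 714.3, so 715.

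**What the 20 counts.** The section does not say whether the 20 are invited, enrolled or analysed.

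| Meaning of 20 | Completers per cluster | Design effect | Needed per arm | Power at 350 |
|---|---|---|---|---|
| Analysed | 20 | 1.95 | 380 | 77% |
| Enrolled | 20 x 0.7 = 14 | 1.65 | 321 | 83% |
| Invited | 20 x 0.49 = 9.8 | 1.44 | 280 | 87% |

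For the enrolled reading at 350: Phi(0.12 / sqrt(0.4536 x 1.65 / 350) - 1.645) = 82.9%.

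**The case against.** The best defence of the power claim has three parts.

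- **The cluster size is ambiguous.** If the 20 are enrolled or invited workers, 350 completers exceed 80% power. This stands as a caveat. Analysed workers is nevertheless the likelier reading, because a design effect of 1.95 is what brings the control-variance formula to 351.6.
- **The 30% to 42% pair is only an example.** For a 12-point rise from 25%, close to the Background's figure of less than a fourth for fruit and vegetable compliance, the need is 352 per arm and power at 350 is 79.8%. This also stands: the gap varies with the base rate. But 30% to 42% is the example the section chose, and it does not fit.
- **The gap is small.** It is about 3 points of power, or half a point in the detectable difference. That is true and limits the importance of the point.

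None of this rescues the sentence about no clustering. It may be a slip for a detectable difference that improves to 9%, but its printed meaning is the reverse.

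A reader might also draw stronger conclusions that the document does not support:

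- **That power is really about 67%.** This is the figure for a two-sided 5% test at 350 per arm (66.5%). The section openly specifies a one-sided test, and the stated hypothesis is directional (the Discussion part of the Abstract). Sidedness is a separate design judgement, not an arithmetic error.
- **That 343 against 350 is a second failure.** It is a 2% difference worth 0.7 points of power, which is rounding.
- **That unequal cluster sizes erode power by a known amount.** The article gives no spread of cluster sizes, so any single figure would be an outside assumption.

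**Conclusion.** The point holds as a correction to the Sample size text. Assuming 20 analysed workers per cluster, equal arms and the stated one-sided 5% test, power for 30% versus 42% at 350 completers per arm is about 77%, not 80%. The detectable difference is about 12.5 points, and about 380 completers per arm would be needed for 12. If about 14 of 20 enrolled workers complete, power is about 83% and the stated 80% is met. It would therefore go too far to say that the design fails to deliver its power.

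The sentence on the absence of clustering is wrong in direction whichever way the 20 is read: the detectable difference decreases to about 9 points. The whole is a minor-to-moderate text correction and does not call the design or analysis into question.

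**What to change.** In Sample size:

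1. State whether the average of 20 per cluster refers to invited, enrolled or analysed workers.
2. If analysed, restate the power for 30% versus 42% as about 77% at 350 completers per arm, or keep 80% power and give the detectable difference as about 12.5 points. If enrolled, show the design effect of 1.65 and the resulting power of about 83%.
3. Replace the stated increase with a decrease to about 9 percentage points when there is no intra-cluster correlation.
4. Say that the 350 applies to each arm, and that 2 x 700 invitations are expected to yield about 343 completers per arm (about 76% power with 20 analysed per cluster).

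No added enrolment and no change to outcomes or analysis are needed. The cost is a slightly less favourable stated figure if the 20 are analysed workers.
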